The DiGest Study is a randomised, double-blind controlled trial of a reduced calorie diet using a novel dietary intervention to assess the benefits of controlling maternal weight gain in late pregnancy in gestational diabetes. The trial is described in detail elsewhere [16]. Briefly, women are randomised to receive a weekly dietbox containing all meals and snacks and are blinded to the overall calorie content (1200 kcal/day for intervention group and 2000 kcal/day for control group; 40% carbohydrate, 25% protein, 35% fat). The dietbox commences at enrolment, typically 28–32 weeks’ gestation, and continues until delivery of the infant. The clinical care team and research team are also blinded to calorie allocation. Dietboxes are nutritionally balanced and low in glycaemic index, low in saturated fat, high in vegetables and protein and suitable for use in pregnancy. Data will be collected to assess the impact upon maternal weight gain, infant birthweight and a range of obstetric and glycaemic outcomes during late pregnancy up to 3 months postnatally [16]. The design of the DiGest trial provides the opportunity for a controlled and blinded dietary study and reduces potential bias due to differences in maternal educational level, cooking ability, income and kitchen facilities.

In this manuscript we describe a follow up study to the DiGest trial which investigates the effect of the reduced calorie dietary intervention in pregnant women upon the development of obesity in a high-risk population of children from birth to 3 years of age. The hypothesis is that a reduced calorie diet in late pregnancy in women with gestational diabetes reduces offspring adiposity and improves maternal weight at 1, 2 and 3 years postpartum.

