## 3. Results

The aim of the study is to investigate the effects of a reduced calorie diet in late pregnancy in women diagnosed with gestational diabetes upon longer-term maternal and offspring metabolic outcomes. The primary outcome for child health is standardised weight at 1, 2 and 3 years of age. The primary outcome for the maternal population is maternal weight at 1, 2 and 3 years postpartum.

Offspring secondary outcomes at 1, 2 and 3 years of age: There are multiple secondary outcomes for children including weight, BMI, growth trajectory, and blood spot biomarkers such as C-peptide or metabolomics at 1, 2 and 3 years. Questionnaire data will be assessed to identify effects of the intervention in pregnancy upon child eating behaviour, with assessment for confounding factors including maternal BMI, maternal eating behaviour and parental feeding style.

Maternal secondary outcomes at 1, 2 and 3 years postpartum: Maternal outcomes to be studied include maternal weight and weight change, BMI, anthropometry measures of adiposity, glycaemia (CGM metrics, HbA1c, OGTT results, indices of insulin production and sensitivity, including HOMA-IR and HOMA-B, Matsuda score and Stumvoll index [34,35], cardiometabolic health (blood pressure, heart rate, lipids, fasting insulin, fasting glucose), maternal food intake, food nutritional content and quality, eating behaviour, quality of life, and incidence of type 2 diabetes or gestational diabetes in a future pregnancy.

Analysis Plan: An intention to treat analysis of the primary outcome for child health (standardised weight at 1, 2 and 3 years of age) will be based on linear regression with adjustment for the stratification variable of study centre through a fixed effects model. The potential role of other explanatory variables such as pre-pregnancy BMI, infant nutrition, infant postnatal growth trajectory or information from the questionnaires will be investigated. A per protocol analysis will also be performed in participants with >80% compliance and at least 4 weeks’ exposure to the intervention. Secondary outcomes will also be examined through regression analyses (linear or logistic) appropriate for the type of outcome being considered.

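### Post-randomisation variables are called confounders, or listed unmarked beside a baseline covariate, in the child analyses; diet-effect models should adjust only for pre-randomisation variables

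*Protocol article*

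**What the plan says.** All of the statements on outcomes and models stand in section 3 (Results) of the protocol article.

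- **Primary child outcome:** "The primary outcome for child health is standardised weight at 1, 2 and 3 years of age".
- **Primary model:** the intention-to-treat analysis "will be based on linear regression with adjustment for the stratification variable of study centre through a fixed effects model". No other covariate is named for it.
- **Next sentence:** it turns to the possible part played by further explanatory variables. The first one named is pre-pregnancy BMI, and the list then runs on: "infant nutrition, infant postnatal growth trajectory or information from the questionnaires will be investigated".
- **Growth as an outcome:** "There are multiple secondary outcomes for children including weight, BMI, growth trajectory", followed by blood spot biomarkers.
- **Child eating behaviour, a secondary outcome:** the aim is put as "Questionnaire data will be assessed to identify effects of the intervention in pregnancy upon child eating behaviour". The rest of that sentence gives three other variables a role in this comparison: "with assessment for confounding factors including maternal BMI, maternal eating behaviour and parental feeding style".

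Two statements elsewhere fix the timing. Section 1 says of the intervention: "The dietbox commences at enrolment, typically 28–32 weeks’ gestation, and continues until delivery of the infant". The Questionnaires paragraph of the methods says that the maternal questionnaires, including the one on eating behaviour, were already in use during the DiGest trial. It then adds the parental feeding style and child eating behaviour questionnaires as new in the follow-up.

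**The concern.** In a randomised comparison, a variable that arises after allocation is not a common cause of arm and outcome. It may lie on the path from diet to outcome, or be a shared consequence of the diet and of other causes of the outcome. Adjusting for it changes the question from the total effect of the pregnancy diet to some partial effect, and it can introduce bias of its own.

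Two statements raise this problem.

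1. The eating-behaviour sentence is about effects of the intervention and gives parental feeding style the role of a confounder. Feeding style is first collected after a diet that ended at delivery. It may also respond to how the child eats.
2. The list of explanatory variables puts growth trajectory and infant nutrition on the same footing as pre-pregnancy BMI. Pre-pregnancy BMI is a legitimate baseline covariate. Growth trajectory shares data with the primary outcome.

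At stake is the meaning of any diet effect reported with such adjustment. It could be read as a refinement of the intention-to-treat result when it answers a different question.

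**Working it through.** **Step 1. Timing of each named variable.**

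| Variable | Named as | Timing on the documents' own account |
|---|---|---|
| Pre-pregnancy BMI | explanatory | before randomisation |
| Infant nutrition | explanatory | after birth |
| Infant postnatal growth trajectory | explanatory, and a secondary outcome | after birth |
| Parental feeding style | confounder (child eating behaviour) | follow-up only |
| Maternal BMI | confounder (child eating behaviour) | not stated; enrolment BMI exists (entry criterion), and BMI is also a maternal outcome at 1, 2 and 3 years |
| Maternal eating behaviour | confounder (child eating behaviour) | not stated; used during DiGest, and also a maternal outcome at 1, 2 and 3 years |

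Three variables are clearly post-randomisation. Two could be either. If taken postnatally, those two are outcomes on which the study itself looks for a diet effect.

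**Step 2. The plan's own power figure.** The Power calculation states 90% power for 0.45 SD and 80% for 0.4 SD with 250 infants, under 20% withdrawal. Assume two-sided alpha 0.05 and 1:1 allocation (the article states neither). Then 250 × 0.8 = 200 are analysed, 100 per arm, and power = Φ(δ√(n/2) − 1.96).

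- 0.45 SD: 0.45 × √50 = 3.18; 3.18 − 1.96 = 1.22; power 88.9%.
- 0.40 SD: 0.40 × √50 = 2.83; 2.83 − 1.96 = 0.87; power 80.7%.

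The stated figures reproduce. They belong to the model without post-randomisation covariates, so this point does not touch them.

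**Step 3. What adding growth would do.** Write weight z-score Y = B + G, where B is birth z-score and G is postnatal change. Assume equal within-arm variances of 0.5 each (so Y has SD 1) and independence of B and G within arm. Let the total effect be d = 0.4 SD, with a share s acting through G.

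- Without G in the model, the arm coefficient is d(1 − s) + ds = d = 0.4.
- With G in the model, the arm coefficient is d(1 − s).

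A simulation of 200 children, 4,000 runs per row, gave:

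| Share s through growth | 0.4 × (1 − s) | Simulated estimate with G | Rejection rate with G |
|---|---|---|---|
| 0% | 0.40 | 0.40 | 97% |
| 25% | 0.30 | 0.31 | 85% |
| 50% | 0.20 | 0.20 | 52% |
| 75% | 0.10 | 0.10 | 16% |
| 100% | 0.00 | 0.00 | 5% |

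Without G the simulated estimate was about 0.40, with about 80% rejection, in every row. The gap between 0.30 and 0.31 is simulation error.

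**Step 4. Distortion as well as attenuation.** In the same model, let the diet lower B by 0.4 and let later catch-up raise G by 0.4. The total effect is −0.4 + 0.4 = 0, yet the arm coefficient with G in the model is −0.4. The adjusted model would report an effect on weight that the children do not show.

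**The case against.** The strongest reply is that the plan already does the right thing where it matters. The primary model holds only arm and centre. Investigating a potential role does not promise an adjusted arm coefficient, still less one ranked above the intention-to-treat result. The Discussion describes a separate aim of weighing pregnancy and postnatal risk factors, and the explanatory-variable sentence can be read as serving it. The confounding label is attached to one secondary outcome only and names neither growth nor infant nutrition. Maternal BMI and eating behaviour may be meant at their pre-randomisation values. Which covariate enters which exploratory model is detail that a condensed article may leave to the full plan.

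Most of this stands. A reader might infer that the plan conditions its primary test on growth or feeding and so removes the effect being tested. The documents do not support that: no post-randomisation variable is placed in the primary model. Nor do they support any single figure for the loss. It runs from none to all of the effect with the mediated share, and with no mediation through growth the adjusted model is even more precise.

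Two things remain. The eating-behaviour sentence concerns effects of the intervention, and feeding style has no pre-randomisation value, so the role given to it is wrong rather than merely unspecified. And the Analysis Plan nowhere marks the work with growth and infant nutrition as exploratory, while it lists growth as an outcome too. With about half of the trial assumed to enter follow-up, there is a fair case for adjustment, but that case is for baseline variables.

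**Conclusion.** The point holds in a limited form. The primary child analysis and its power statement are unaffected. The plan misassigns parental feeding style as a confounder of a randomised effect, leaves maternal BMI and eating behaviour in that role without restricting them to pre-randomisation values, and mixes baseline with post-randomisation explanatory variables, one of which is also an outcome.

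If a diet effect were reported with adjustment for growth, a true 0.4 SD could appear as anything from 0.40 to 0 SD under the illustrated model. This rests on an assumed mediated share, equal variances, and independence of birth size and later change. It shows the mechanism and does not forecast this trial. The size for child eating behaviour cannot be worked out, because the documents give no figures for that outcome.

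**What to change.** Three changes of wording in section 3:

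1. State that every model estimating the diet effect, including the one for child eating behaviour, adjusts only for centre and prespecified variables measured before randomisation. Examples are pre-pregnancy or enrolment BMI, and baseline maternal eating behaviour if it was collected then.
2. Label models containing infant nutrition, growth trajectory, parental feeding style or postnatal maternal measures as exploratory mediation or risk-factor analyses, reported apart from the randomised comparison.
3. Do not call those variables confounders of the randomised effect, and give the time of measurement wherever maternal BMI or eating behaviour is used as a covariate.

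The cost is text only. No data collection changes, no planned analysis is lost, and the sample size stays as it is.

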## 2. Materials and Methods

Study design and ethical approval: The DiGest Follow up study is an observational study on the effects of a multicentre, prospective, randomised double-blind controlled dietary intervention trial conducted in late pregnancy. In summary, participants of the follow up study will have been exposed to either the intervention diet of 1200 kcal/day, or the control diet of 2000 kcal/day as part of the DiGest study. Macronutrient ratios were identical for each diet; 40% carbohydrate, 25% protein, 35% fat. Meals were prepared from the same recipes, with a factor of 1.667 used to convert portion size to obtain meals of two different sizes. This diet it provided from enrolment (typically 28–32 weeks’ gestation) to delivery of the infant. Participants will have attended 4 study visits in total to provide blood samples, blood pressure, body weight and anthropometry measurements, and to complete a series of questionnaires. Randomisation for the original DiGest study was stratified for centre. Throughout the DiGest intervention and Follow-up study, both mothers and children will receive standard NHS care, as described in the NICE guidelines [17]. The study is being conducted in accordance with the Declaration of Helsinki, and the protocol has been submitted to the Research Ethics Committee (UK Bloomsbury REC 21/PR/0213) and the NHS Health Research Authority (IRAS 281062).

Recruitment: The DiGest trial recruitment occurs at 5 hospital trusts in East Anglia, UK. The same study sites will be used for the follow-up study. At 3 months postpartum, DiGest trial participants will be given information about the follow-up study and invited to participate by the research midwives, nurses, clinical research staff or by their physician/obstetrician. For training purposes, students in healthcare disciplines (e.g., medicine, biomedical science, nursing, midwifery) may also occasionally recruit patients under appropriate supervision. Informed consent will be obtained at the final visit of the DiGest dietary intervention, with the mothers providing consent on their infant’s behalf. Participants (or mother-infant dyad) can withdraw from the study at any time without reason without affecting their clinical care. There is no financial incentive for this study, but a small token of appreciation is provided for the child at each visit in line with guidelines of the Royal College of Paediatrics and Child Health [18].

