Eligibility criteria: All women from the DiGest cohort (confirmed gestational diabetes and BMI 25 kg/m^2^ or above at enrolment) are eligible to enrol in the follow-up study, however, they must be recruited within 12 months of the baby’s birth. Mothers would be excluded if they are unwilling or unable to provide informed consent, if they experienced stillbirth, neonatal death or had an infant born with severe congenital anomaly.

Follow-up visit structure: The study timeline is outlined in Figure 1. Study visits will be carried out in the participants’ home, local hospital or at another place convenient for the participant. The initial follow-up visit will coincide with the final DiGest visit at 3 months after the birth, where the consent form will be signed for both the mother and infant. Maternal and infant anthropometry will be measured at this visit as part of the DiGest study. Further Follow-up visits will take place at 1, 2 and 3 years postnatally and will take approximately 45 min.

Anthropometry Measurements: At all visits, maternal height and weight will be measured using a routinely calibrated stadiometer and weight scale (Seca Hammer Steindamm, Birmingham, U.K.). Waist and hip circumference will be measured to the nearest 0.1 cm with a fibreglass tape, in accordance with the World Health Organisation criteria [19]. Waist circumference is located at the midpoint between the lowest palpable rib and the iliac crest. Hip circumference is measured at the greater trochanters, or at the widest extension of the buttocks. Other maternal anthropometry that will be measured include mid upper arm circumference and skinfold thickness, using Harpenden calipers recorded to the nearest 0.2 mm. Infant length and weight will be taken in a supine position, measured to the nearest 0.1 cm using fibreglass tape, and 0.01 kg using scales (SECA 757 Infant digital scale, Seca, Birmingham, UK). Infant abdominal circumference, head circumference, skinfold thickness (Holtain calipers, Crosswell, Wales, U.K.), mid upper arm circumference will also be measured by trained research staff according to methods described elsewhere [16]. All equipment used to measure anthropometry are routinely calibrated.

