Power calculation: All eligible women and their infants will be invited to join the follow-up study. However, calculations are based on assuming a 50% recruitment rate (*n* = 250 women and their infants) and a 20% withdrawal rate. For the maternal primary endpoint, data from earlier work suggest that typical values for maternal BMI outside of pregnancy in women with a history of gestational diabetes is mean 28.7 kg/m^2^ (SD 7.1; *n* = 416) and maternal postpartum HbA1c 37.5 mmol/mol (SD 7.5; *n* = 157) [36]. Using these figures, recruitment of 250 women, will give 90% power to identify a 3 kg/m^2^ difference in BMI (e.g., 29 vs. 32 kg/m^2^) and a 3 mmol/mol difference in HbA1c postnatally while allowing for a 10–20% withdrawal rate. At 80% power, this sample size is sufficient to identify a 2 kg/m^2^ difference in BMI (e.g., 30 vs. 32 kg/m^2^) and a 2 mmol/mol difference in HbA1c postnatally.

For the offspring primary endpoint, assessment of infant weight will be based upon z-(SD) scores. At the sample size of 250 infants, there will be 90% power to identify a 0.45 SD increase in weight with 80% power to identify 0.4 SD increase in weight. At the age of 2 years old, a z-score of 0.4 is equivalent to 0.5 kg.

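### Maternal weight is the primary outcome, but the power stated for it covers only BMI and HbA1c, uses a between-woman SD that ignores enrolment weight, and does not deliver 80% power for 2 kg/m²

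*Protocol article*

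**What the plan says.** The outcome definitions in section 3 (Results) of the protocol article state: "The primary outcome for the maternal population is maternal weight at 1, 2 and 3 years postpartum". The list of maternal secondary outcomes that follows includes BMI and HbA1c, and also weight and weight change.

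The power paragraph in the same section begins "For the maternal primary endpoint, data from earlier work suggest that typical values for maternal BMI outside of pregnancy" and gives two sets of planning values: for BMI, "mean 28.7 kg/m^2^ (SD 7.1; *n* = 416"), and for HbA1c, "maternal postpartum HbA1c 37.5 mmol/mol (SD 7.5; *n* = 157"). From these it claims that 250 women "will give 90% power to identify a 3 kg/m^2^ difference in BMI", and 3 mmol/mol in HbA1c, after 10–20% withdrawal. It adds: "At 80% power, this sample size is sufficient to identify a 2 kg/m^2^ difference in BMI", with 2 mmol/mol for HbA1c. Weight in kilograms does not appear in the maternal part of the calculation.

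On earlier weight, section 2 (Materials and Methods) gives the entry criterion as "confirmed gestational diabetes and BMI 25 kg/m^2^ or above at enrolment", and says of the parent trial: "Participants will have attended 4 study visits in total to provide blood samples, blood pressure, body weight and anthropometry measurements".

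The analysis plan paragraph describes a centre-adjusted linear regression for the child primary outcome. It sets out no model for maternal weight.

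**The concern.** There are three linked problems.

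- **The power belongs to other endpoints.** A reader who wants to know what difference in maternal weight the study can detect finds no answer. BMI is a near relative of weight; HbA1c is not, and its power says nothing about weight.
- **The SD is the spread between women at one time.** Most of that spread was there before the diet began. Weight or BMI at enrolment is known for every woman, and conditioning on it would remove much of the spread. The power calculation does not do so.
- **The two BMI claims do not fit together or fit the stated SD.** A smaller difference is said to be detectable than the sample size allows.

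At stake is how a null maternal result would be read. Taken at face value, the paragraph says that 2 kg/m² would probably have been found. On its own inputs, the chance is not much better than even.

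**Working it through.** **Inputs from the article:** SD of BMI 7.1 kg/m²; SD of HbA1c 7.5 mmol/mol; 250 women; withdrawal of 10–20%, leaving 225 or 200.

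**Assumed, because not stated:** two-sided alpha 0.05; 1:1 allocation; normal approximation; maternal height 1.55–1.70 m (1.63 m as a single value); correlation r of 0.7–0.9 between earlier and later weight.

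**Step 1: reproduce the stated power.** With N women in total, power = Φ(δ / (SD × √(4/N)) − 1.960). For BMI, δ = 2 and N = 200: 2 / (7.1 × 0.1414) = 1.992, and Φ(0.032) = 51%.

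| Difference | N = 250 | N = 225 | N = 200 | Stated |
|---|---|---|---|---|
| BMI 3 kg/m² | 91.6% | 88.7% | 84.8% | 90% |
| BMI 2 kg/m² | 60.5% | 56.1% | 51.3% | 80% |
| HbA1c 3 mmol/mol | 88.5% | 85.1% | 80.7% | 90% |
| HbA1c 2 mmol/mol | 55.9% | 51.6% | 47.0% | 80% |

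The 3 kg/m² claim is met with no withdrawal, nearly met at 10%, and missed at 20%. The 2 kg/m² claim fails at every N. A one-sided test would rescue the first (91.0% with 200) but not the second (64% with 200, 72% with 250).

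**Step 2: compare the two BMI claims with each other.** For one sample size and SD, the difference detectable at 80% power is a fixed fraction of that at 90%: (1.960 + 0.842) / (1.960 + 1.282) = 0.864. If 3 kg/m² is the 90% figure, the 80% figure is 3 × 0.864 = 2.6 kg/m², not 2. This does not depend on the SD or on withdrawal.

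**Step 3: what 2 kg/m² would need.** N = 4 × (2.802 × 7.1 / 2)² = 396 completers, or 396 / 0.8 = 495 recruited at 20% withdrawal. Alternatively, an SD of 5.64 with 250 women or 5.05 with 200.

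**Step 4: detectable difference on the stated basis.** With 200 completers:

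- 80% power: 2.802 × 7.1 × √(4/200) = 2.81 kg/m².
- 90% power: 3.242 × 7.1 × √(4/200) = 3.25 kg/m².

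Multiplying by height squared (2.40 to 2.89 m²) gives 6.8–8.1 kg at 80% and 7.8–9.4 kg at 90%. The article's own 3 kg/m² is 7.2–8.7 kg.

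**Step 5: effect of conditioning on an earlier weight.** The residual SD is 7.1 × √(1 − r²). With 200 completers at 80% power, and kg at 1.63 m:

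| Assumed r | √(1 − r²) | kg/m² | kg |
|---|---|---|---|
| 0 (as stated) | 1 | 2.81 | 7.5 |
| 0.7 | 0.714 | 2.01 | 5.3 |
| 0.8 | 0.600 | 1.69 | 4.5 |
| 0.9 | 0.436 | 1.23 | 3.3 |

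**The case against.** The strongest reply is that this is a condensed article and that covariates for one outcome are normally left to the full protocol or analysis plan. The centre-adjusted model is given for the child outcome, and nothing is said of maternal weight. A reader might infer that the maternal analysis will be unadjusted, that enrolment weight is therefore wasted, and that about 8 kg is all the study can detect. The documents do not support that. A cross-sectional SD is a planning choice; if the analysis adjusts for baseline, the calculation is merely conservative. Weight change is listed as a maternal secondary outcome, so some earlier weight will be used.

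It can also be said that BMI is weight divided by a nearly constant height squared, so BMI is a fair planning surrogate. That stands in part, but it leaves the reader without a target in kg and does nothing for HbA1c.

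The gain from adjustment is uncertain. Enrolment weight is taken in late pregnancy, outcomes come 1–3 years later, and further pregnancies may intervene, so r could be lower than assumed. The SD comes from women with mean BMI 28.7 kg/m², whereas this cohort was restricted to 25 kg/m² or above, so its spread may differ.

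None of this answers the mismatch between outcome and power, or the 2 kg/m² figure. The paragraph says it uses the quoted SDs. An unstated adjustment at r = 0.7 would give about 80% power for 2 kg/m² with 200 women, but the 3 kg/m² claim would then be far too modest at 90%, where the detectable difference would be 2.3 kg/m².

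**Conclusion.** The point holds in this form: the power offered for the maternal primary endpoint belongs to two secondary outcomes, rests on a between-woman SD that ignores a baseline measure already held, and overstates the power for 2 kg/m².

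The firmest part is numerical: 51–61% in place of 80% for 2 kg/m², and about 85% in place of 90% for 3 kg/m² at the upper withdrawal rate. It rests on the article's own SD and sample size, with two-sided 0.05 and equal allocation assumed. The mismatch of endpoints needs no assumption. The kg values depend on an assumed height, and the gain from adjustment on an assumed correlation, so both should be read as ranges.

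The finding concerns the power calculation. It does not show that the eventual analysis omits baseline weight. Nor does it show that a realistic effect would be missed, since the article gives no expected maternal effect.

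**What to change.** 1. Specify the maternal primary analysis as a regression or mixed model for weight, with enrolment (or pre-pregnancy) weight and centre as covariates.
2. Restate power for weight in kg, using a residual SD and showing a range of correlations. With 200 completers at 80% power, r from 0.7 to 0.9 would give about 5.3 down to 3.3 kg at 1.63 m. The parent trial's own weights could supply the SD and, from its later visits, a guide to r.
3. Correct the 2 kg/m² statement. Without adjustment, the 80% figure is about 2.5 kg/m² with 250 women and 2.8 kg/m² with 200. Qualify the 90% claim for 3 kg/m² at 20% withdrawal, and revise the HbA1c claims in the same way.
4. Label the BMI and HbA1c power as relating to secondary outcomes, and remove weight itself from the maternal secondary list.

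The cost is wording and an analysis specification. No new visit, measurement or participant is needed.

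### 250 women do not give 80% power for a 2 kg/m² BMI or 2 mmol/mol HbA1c difference: about 60% and 56% at best two-sided, 51% and 47% after 20% withdrawal

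*Protocol article*

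**What the plan says.** The power calculation, in section 3 (Results) of the Protocol article, is made "assuming a 50% recruitment rate (*n* = 250 women and their infants) and a 20% withdrawal rate". For the maternal endpoint it takes two spreads from earlier work: BMI "mean 28.7 kg/m^2^ (SD 7.1; *n* = 416" and "maternal postpartum HbA1c 37.5 mmol/mol (SD 7.5; *n* = 157".

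From these inputs it makes two pairs of statements:

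- **90% power:** "recruitment of 250 women, will give 90% power to identify a 3 kg/m^2^ difference in BMI", and also for "a 3 mmol/mol difference in HbA1c postnatally while allowing for a 10–20% withdrawal rate".
- **80% power:** "At 80% power, this sample size is sufficient to identify a 2 kg/m^2^ difference in BMI", and also for "a 2 mmol/mol difference in HbA1c postnatally".

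The BMI statements come with worked pairs of means that are exactly 3 and exactly 2 kg/m² apart. The paragraph gives no alpha, sidedness or allocation ratio. The second pair does not mention withdrawal.

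**The concern.** All the inputs for a check are in the paragraph, and the text presents the power figures as following from them. A difference of 2 is only 2/7.1 = 0.28 SD for BMI and 2/7.5 = 0.27 SD for HbA1c. With about 100 to 125 women per arm, effects that small do not have 80% power. The step from 3 units at 90% power to 2 units at 80% power is also too large for a single sample size.

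What is at stake is how a null maternal result is read. A reader told that power was 80% would expect a true 2-unit difference to be missed one time in five, and would take a null finding as fair evidence against it. On the article's own inputs (two-sided 5%, equal arms) it would be missed 40–44% of the time with all 250 women analysed, and about half the time with 200.

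**Working it through.** **Inputs from the article.** 250 women in total; withdrawal of 20% (opening assumption) or 10–20% (90% sentence), leaving 200 or 225; SD 7.1 kg/m² and 7.5 mmol/mol; differences of 2 and 3 units.

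**Assumed, not stated.** Two-sample comparison of means, two-sided 5%, 1:1 allocation. One-sided 5% is tried as well.

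**Formula** (normal approximation, N = total analysed):

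power ≈ Φ( Δ / (SD × √(4/N)) − z), with z = 1.960 two-sided or 1.645 one-sided.

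**Step 1: the 90% figure, all 250 analysed.** √(4/250) = 0.1265.
- BMI: 3/(7.1 × 0.1265) = 3.340; 3.340 − 1.960 = 1.380; power 91.6%.
- HbA1c: 3/(7.5 × 0.1265) = 3.162; 3.162 − 1.960 = 1.202; power 88.5%.

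So the 90% figure is reproduced for BMI, and nearly for HbA1c, when nobody withdraws.

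**Step 2: the 80% figure, same N.**
- BMI: 2/(7.1 × 0.1265) = 2.227; 2.227 − 1.960 = 0.267; power 60.5%.
- HbA1c: 2/(7.5 × 0.1265) = 2.108; 2.108 − 1.960 = 0.148; power 55.9%.

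The 80% figure is not reproduced for either.

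**Step 3: take off withdrawal and vary sidedness.** The table uses the noncentral t distribution, which is within 0.4 points of the approximation.

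| Difference | Stated | Two-sided 5%: N = 250 / 225 / 200 | One-sided 5%: N = 250 / 225 / 200 |
|---|---|---|---|
| 2 kg/m² | 80% | 60 / 56 / 51% | 72 / 68 / 63% |
| 2 mmol/mol | 80% | 56 / 51 / 47% | 68 / 64 / 59% |
| 3 kg/m² | 90% | 91 / 88 / 84% | 95 / 94 / 91% |
| 3 mmol/mol | 90% | 88 / 85 / 80% | 93 / 91 / 88% |

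No cell in the 2-unit rows reaches 80%. Unequal allocation makes it worse: at 2:1 with 250 analysed, the two-sided figures are 56% and 51%. Two-sided 80% power for 2 units would need about 398 (BMI) and 444 (HbA1c) women analysed.

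**Step 4: which convention did the authors use?** The offspring figures in the same section (0.4 SD at 80%, 0.45 SD at 90%) offer a check. With 200 analysed in total, two-sided 5% gives Φ(0.4/√(4/200) − 1.960) = Φ(0.868) = 80.7%, and Φ(0.45/√(4/200) − 1.960) = Φ(1.222) = 88.9%. Both fit. One-sided 5% at 200 would give Φ(2.828 − 1.645) = 88% for 0.4 SD, which does not. Two-sided 5% with 200 analysed is therefore the likelier basis, though the article does not say so.

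**Step 5: consistency of the two statements.** At one N and SD, the detectable differences at 90% and 80% power stand in the ratio (1.960 + 1.282)/(1.960 + 0.842) = 1.16 (one-sided: 2.927/2.487 = 1.18). The maternal figures give 3/2 = 1.5; the offspring figures give 0.45/0.40 = 1.125. Read as exact detectable differences, 3 units at 90% implies 3/1.16 ≈ 2.6 units at 80%, not 2.

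**Step 6: detectable differences with 100 per arm, two-sided 5%.** These are 0.398 SD at 80% power and 0.461 SD at 90% power.
- BMI: 0.398 × 7.1 = 2.8 and 0.461 × 7.1 = 3.3 kg/m².
- HbA1c: 0.398 × 7.5 = 3.0 and 0.461 × 7.5 = 3.5 mmol/mol.

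**The case against.** **The 90% claim.** A reader might infer that it is plainly wrong too. The article does not support saying that without conditions. Sidedness is unstated, and a one-sided 5% test with 200 women gives 91% and 88%. Even two-sided, BMI at 10% withdrawal is 88%, close to the claim. What stands is conditional: under two-sided 5%, the claim is not met at 20% withdrawal for either measure, nor at 10% for HbA1c (85%).

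**The ratio.** A reader might also infer that the two BMI statements cannot both be true at any sample size. That holds only if both are exact detectable differences. If they mean at least 80% and at least 90%, about 400 women analysed would satisfy both for BMI (80% and 99%). Rounding to whole units can also turn a ratio of 1.16 into 3 and 2. Neither makes a true 2-unit difference 80% powered with 250 women, but the ratio is supporting evidence and not the proof.

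**Other rescues.** If 250 were per arm, 200 analysed per arm would give 80% for 2 kg/m² (76% for HbA1c). But the article gives 250 as the total at 50% recruitment, and its offspring figures fit 200 in total. Adjustment for a baseline value would raise power, but 80% would need a baseline correlation of about 0.61 (BMI) to 0.66 (HbA1c) with 250 analysed, or 0.70 to 0.74 with 200. No correlation is stated, and the text works from the raw SDs.

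**Importance.** All eligible women are invited, so the calculation caps nothing. The named maternal primary outcome is weight, with BMI and glycaemia listed as secondary. That is fair, but the power section presents these figures as the case for the maternal primary endpoint.

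**Conclusion.** The concern holds for the 80% statement. On the article's own SDs and total of 250, with two-sided 5% and equal arms, power is overstated by 20 points (BMI) and 24 points (HbA1c) with nobody lost, and by 29 and 33 points at 20% withdrawal. The conclusion does not hang on the unstated sidedness or allocation: the most favourable convention tried, one-sided 5% with no withdrawal, stops at 72% and 68%.

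The 90% statement is not shown to be wrong outright. It fails at 20% withdrawal (84% and 80%) if the test is two-sided 5%, which is the likelier reading given the offspring figures. The two statements are inconsistent only when read as exact detectable differences.

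None of this shows that the study must recruit more women. It shows that the stated sensitivity for the maternal outcomes is too favourable.

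**What to change.** In the power calculation of the Protocol article:

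1. State alpha, sidedness and allocation ratio, and use one withdrawal figure throughout.
2. Delete the claims of 80% power for 2 kg/m² and 2 mmol/mol.
3. Restate both power levels for 200 evaluable women (250 less 20%). If the basis is two-sided 5% and 1:1, this reads: 80% power for about 2.8 kg/m² and 3.0 mmol/mol; 90% power for about 3.3 kg/m² and 3.5 mmol/mol. If the authors used another basis, the figures should be recomputed on it and the basis given.
4. If the claim was meant to rely on baseline adjustment, give the assumed correlation and its source.

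The cost is a change of wording and less favourable stated detectable differences. Recruitment, visits and analysis are unaffected.
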